### Trial status

Trial registration number: NCT04978064 (S1 File). Protocol version 1.0, 20 April 2021. The proposed start date of randomised participant recruitment: September, 2021. The proposed project recruitment completion date of any participant including those not randomised: September, 2022. The proposed end of follow-up of all participants including those randomised: September, 2022.

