### Recruitment: Consent procedures

In advance, a written, informed consent (in Spain the informed consent will be oral and recorded) for administering the screening of IPV, will be sought from the pregnant women at the first antenatal visit with a midwife. Those who screen positive, will also be asked for consent to receive the e-health package intervention and to complete baseline and outcome measurement questionnaires (one month after the intervention). For the pilot trial, women who consent to receive the e-health package will be randomized (following a modified Zelen’s design) into the intervention group (without their knowledge) or into the control group. Women in the control group will additionally be asked for a second informed consent, to be allocated in this group and to receive the e-health package 8 weeks later. This approach is suggested by the input of IPV survivors. A few women from the intervention and control groups of the pilot trial will be asked for consent to be contacted for a qualitative interview. Women will be informed that they have the right to refuse participation as well as to withdraw their consent at any time, without giving a reason, and that this will not affect their subsequent care. If they withdraw consent, data collected up to the point of withdrawal will be retained in the study. Participant information sheets and consent forms used for this pilot study are available on request from investigators. The informed consent provides study aims, contact details and sources for further information. Given the importance of taking into consideration the views and opinion of the participants [25], all recruitment materials have been developed with significant input from a patient and public involvement (PPI) group consisting at two participant representatives from Spain and Denmark (see the Discussion section).

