### Study interventions and assessments

Intervention group: Women positive for IPV who accept the e-Health intervention and who have been randomly allocated in the intervention group will receive the e-health package as the rest of the cohort, as well as the baseline and outcome measurements. The e-health package will include six video counselling sessions by trained providers—a psychologist in Spain; midwives in Denmark. Women in both countries will be provided access to a mobile app for designing security plans. This will be an adapted version of the mobile app “My Plan”. To organize and host the video counselling sessions the platform “Linkello Medical” will be used in Spain and the app “My Hospital” will be used in Denmark. Both allow health providers to interact with the women in the place they prefer as long as they have Internet connection. In “Linkello Medical”, the psychologist will send an Internet link to the women by her preferred means (via mobile message or by email) and she would just have to click on the link to connect. Women will not need to register nor provide any personal data. The link will be volatile, i.e., it will be not reusable after completion of the communication. In “My Hospital”, is a software developed specifically for confidential hospital-patient communication in the Region of Southern Denmark and is already used in antenatal care as a regular communication tool. When the pregnant woman attend her first antenatal care visit, she will be introduced to My Hospital and instructed in how to access the system via the Internet or a mobile app. The midwives book the women for a video call through the system. Fifteen minutes before the video call is starting, the woman receives a notification to accept the call. Once the woman has accepted the call, the midwife can start the video consultation. This easy and confidential way of interaction will facilitate women’s participation. The mobile app for safety planning will be camouflaged to look like a common pregnancy app. The content and setup of the safety planning app was adapted from the interactive safety decision aid developed by Glass, et al. [26] which is freely available. A safety plan is a personal and practical plan, designed by a woman exposed to violence to minimize their risk of danger and exposure to violence. By digitalizing the safety plan into an app, the women will always have it available to remind them of their own strategies and resources. The safety planning element will be hidden inside the pregnancy app for security reasons; the women must log on for this element to be opened. Once a woman has logged on, the front page consists of two buttons, “Help” and “Emergency”. Both buttons consist of default contact information for relevant resources which can help a woman in case she needs help or is in an emergency situation. The woman can edit the information to fit her own needs. The app also includes the following features: “Warning signs”, where the woman can add signs that may trigger situations where violence could occur; “Strategies”‘, where the woman can note down her coping strategies; and, “Diary”, where a woman can write down anything of importance. It will also contain the feature “Knowledge about domestic violence” which will provide information and links to local and national resource’s relevant for women exposed to violence. Under another feature called “Quick Messages” a woman can enable a predetermined message to her emergency contacts. In case the woman needs to exit the app quickly, she will be able to press the “Quick-exit” button, where she will immediately return to the camouflaged part of the app. This app has been made freely downloadable to researchers and users for both android and iOS devices.

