
We will monitor if participants adhere to all the sessions offered for counselling and in case of non-adherence or failure to engage in counselling, the counsellor will follow specific protocol to encourage reengagement. In Spain, the psychologist will contact the woman two to three times through the preferred mean (email or phone). In Denmark, a project midwife will try to contact the woman on the preferred mean (email or phone) at 3 occasions within 6 weeks. The content of the six individually tailored sessions will be based on the Dutton’s Empowerment Model [27] and the Psychosocial Readiness Model [28]. Specifically, the contents will include (session 1) the evaluation of abusive behaviour (which will also served to protect the pregnant women is the level of violence detected is high); (session 2) safety planning, network and resources; (session 3) psycho-education (healthy relationships, cycle of violence…); (session 4) self-esteem and self-care and (sessions 5 & 6) empowerment, choice making and problem solving. The video consultations will be planned for every 2 weeks at a time where the women feel comfortable. However, schedule flexibility will always prevail to promote women participation. Criteria for discontinuing or modifying allocated interventions will be applied to women with an elevated risk for IPV who will be routinely treated according to the standard protocol in each country. In other words, if during the interventions the health providers detect an increased on the level of violence, they will apply the established national protocols to protect the pregnant women.

Control group: IPV positive women who accept the e-Health intervention package will be asked for a second consent to receive a delayed intervention (8 weeks later) and to complete the baseline and outcome measurements. Women can request to leave the control group at any time and receive the intervention immediately (in which case the data will be part of the cohort study).

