#### Progression criteria

Table 1 outlines the main criteria that will be considered to assess the feasibility of a full-scale RCT. In addition, our qualitative findings will also be used to support the decision-making around progression to a full-scale trial. For example, if a progression criterion outlined in Table 1 does not meet the threshold for progression, but we have developed a qualitative understanding of why this occurred and how it could be improved, then it may still be possible to proceed with the full trial. The research team of the STOP project will have access to these interim results.

**Table 1 pone.0282997.t001:** Suggested progression criteria in eIPV trial.

Feasibility objectives and related data to be collected	Go criteria to proceed to full trial	Criteria to reassess and adjust full trial protocol	Stop criteria
Study population			
1. Consent rate of eligible women	Rate >25% of eligible women agreeing to participate.	Rate between 11% and 24% women agreeing to participate	Rate <10% of eligible women agreeing to participate
Study outcomes			
2. Proportion of women in either intervention or control group for whom the allocated treatment is adhered to.	Adherence to allocated treatment in >80% of study sample.	Adherence to allocated treatment in between 51% and 79% of study sample.	Adherence to allocated treatment in <50% of study sample.
RCT process			
3. Collection of data on clinical outcomes	Complete data available of >80% of study sample.	Missing data between 21% and 49% of study sample.	Data missing of >50% of study sample.

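### Recruitment and follow-up both end in September 2022, but the stated schedule needs about 14 weeks to the outcome questionnaire (about 22 for controls if theirs follows the delayed package), so the two dates cannot both hold

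*Protocol article*

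**What the plan says.** All references are to the protocol article.

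- **Calendar (Trial status).** Randomised recruitment opens in September 2021: "The proposed start date of randomised participant recruitment: September, 2021". Recruitment of everyone closes a year later: "The proposed project recruitment completion date of any participant including those not randomised: September, 2022". Follow-up closes in that same month: "The proposed end of follow-up of all participants including those randomised: September, 2022".
- **Length of the package (Study interventions and assessments).** "The e-health package will include six video counselling sessions by trained providers". On spacing: "The video consultations will be planned for every 2 weeks at a time where the women feel comfortable". The same section adds that "schedule flexibility will always prevail to promote women participation", so the planned course can run longer.
- **Outcome timing (Recruitment: Consent procedures).** Women who screen positive are asked for consent to the package and "to complete baseline and outcome measurement questionnaires (one month after the intervention").
- **Controls (same section).** They are asked to accept the package 8 weeks later. The text gives no separate control timepoint for the outcome; the schedule figure is not available here.
- **Randomised sample (Eligibility criteria).** 20 women, 5 per arm in each country. The number of days needed to fill it is a secondary outcome. No separate closing date for randomisation is given.
- **Progression criterion 3 (Table 1).** Go requires "Complete data available of >80% of study sample".

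**The concern.** If the last woman can be recruited in the month in which follow-up of all participants stops, her outcome questionnaire falls due after the study has closed. Her data are then absent because of the calendar, not because she withdrew or could not be reached.

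This matters because completeness of outcome data is one of the things the pilot sets out to measure. It is a secondary outcome in each arm and it drives criterion 3. With 20 women, a few outcomes cut off by the closing date could make data collection look less feasible than it is. Table 1 does not separate an outcome that was not yet due from one that was lost.

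**Working it through.** **Path length, from the stated schedule**

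- First to sixth session: (6 − 1) × 2 = 10 weeks. Counting six full two-week blocks gives 12.
- Outcome one month later: about 4 weeks.
- Intervention arm and cohort: 10 + 4 = 14 weeks (16 with a 12-week course).
- Controls, if the outcome follows the delayed package: 8 + 10 + 4 = 22 weeks (24 with a 12-week course).
- Controls, if the outcome is instead taken when the delay ends (an assumption): 8 weeks.

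These counts start the first session on the day of entry and allow no slippage.

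**Can both dates hold?** The article gives months only. On the most lenient reading, recruitment closes on 1 September 2022 and follow-up on 30 September 2022, a gap of 29 days. The 14-week path needs 98 days, so the shortfall is 98 − 29 = 69 days, about 10 weeks. If both dates are the same day, the shortfall is the full 14 weeks. No reading of the two months removes the conflict.

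**Cut-off dates**

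| Path | Weeks | Latest entry if follow-up ends 30 Sep 2022 | Latest entry if it ends 1 Sep 2022 | Follow-up end needed if recruitment runs to 30 Sep 2022 |
|---|---|---|---|---|
| Intervention, cohort | 14 | 24 Jun 2022 | 26 May 2022 | 6 Jan 2023 |
| Same, 12-week course | 16 | 10 Jun 2022 | 12 May 2022 | 20 Jan 2023 |
| Control, outcome after delayed package | 22 | 29 Apr 2022 | 31 Mar 2022 | 3 Mar 2023 |
| Same, 12-week course | 24 | 15 Apr 2022 | 17 Mar 2022 | 17 Mar 2023 |
| Control, outcome at end of delay | 8 | 5 Aug 2022 | 7 Jul 2022 | 25 Nov 2022 |

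The day-level dates only carry the arithmetic; read them as late June, late April and so on.

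**What criterion 3 can absorb.** If the criterion is applied to the 20 randomised women, 16/20 is exactly 80% and does not exceed it, so Go needs at least 17. Up to three women may lack data, and a fourth loses Go.

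**Dependence on when the 20 enter.** The article gives no recruitment rate, so these are scenarios, not estimates. All assume follow-up to 30 September 2022 and no other loss.

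- All 20 randomised by late April 2022, about 8 months after 1 September 2021: 20 of 20 can complete.
- Even entry over 1 September 2021 to 30 September 2022 (394 days), controls on 22 weeks: intervention 1 − 98/394 = 0.751, control 1 − 154/394 = 0.609. Expected complete: 10 × 0.751 + 10 × 0.609 = 13.6 of 20 (68%). The chance of at least 17 is about 0.07.
- Even entry, controls assessed at week 8: control 1 − 56/394 = 0.858. Expected complete: 7.51 + 8.58 = 16.1 of 20 (about 80%). The chance of at least 17 is about 0.43.

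The effect on the criterion therefore runs from none to large, depending on facts that the article does not give.

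**The case against.** The strongest reply is that the September 2022 recruitment date belongs to the whole cohort, since it expressly includes women who are not randomised. Only 20 women are randomised, acceptors are identified daily, and the sample closes when filled. Nothing says that those 20 are spread over 13 months.

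This stands, and it rules out two stronger readings that a reader might infer:

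- **That criterion 3 is depressed by the calendar.** This is possible but not established. It needs some of the 20 to enter late, or criterion 3 to be applied to the whole cohort; Table 1 does not define the sample further. Nor does the text say that an outcome not yet due counts as missing. Its remark on failure to obtain data follows a description of attempts to reach unreachable women.
- **That the loss falls more heavily on controls.** This holds only on the 22-week path. The text implies that path but does not fix it. If controls are assessed when the delay ends, their path is 8 weeks against 14, and the imbalance reverses.

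Two further replies have some force. The dates are only proposed. The criteria are labelled as suggested, and the article lets the team proceed after a missed threshold if the reason is understood and could be remedied. Both soften the consequence, but neither makes the dates compatible. On the other side, control places may fill last, because women who decline the delay are replaced until the required number is reached. Late entry among controls is therefore plausible, though it cannot be quantified.

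**Conclusion.** The conflict of dates is certain. Recruitment of any participant and follow-up of all participants cannot both end in September 2022 when the shortest path through the package to its outcome is about 14 weeks. Cohort women recruited in about the last 14 weeks (about 10 on the most lenient reading of the months) cannot give an outcome.

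The consequence for the randomised comparison is conditional. It arises for women entering after about late June 2022 (intervention) or about late April 2022 (controls, 22-week path), taking follow-up to the end of September 2022. It vanishes if all 20 are randomised by late April 2022. The 22 weeks rest on the control outcome following the delayed package. No size for the effect on criterion 3 can be derived from the article.

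The point deserves correction because, followed literally, the plan cuts off late entrants' outcomes, and a criterion resting on 20 women has room for only three missing.

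**What to change.** 1. Reconcile the dates in Trial status in one of two ways:
   - Keep the end of follow-up and state separate closing dates for randomisation and for cohort recruitment, each earlier than it by the full path. For follow-up to the end of September 2022, that is about late June 2022 for the 14-week path and about late April 2022 for randomisation if controls are on the 22-week path.
   - Keep recruitment to September 2022 and move the end of follow-up to about early January 2023 for the 14-week path, or about early March 2023 if controls on the 22-week path may enter until then.
2. State in the text when the control outcome is measured, since this decides which path applies.
3. In criterion 3 and the completeness outcomes, report outcomes not yet due at closure separately from dropout and failed contact.

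The first option costs recruitment time: about 8 months to fill the 20 places instead of about 13. If they are not filled by then, recruitment duration should be reported as not reached. The second costs up to about 22 weeks (some 5 months) of further follow-up for the last women. Items 2 and 3 cost a sentence each.

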### Confidentiality

In order to protect confidentiality before, during, and after the trial, personal information about potential and enrolled participants will be collected and saved during the screening process in a secured data base and it will be only accessed by authorised research investigators of the STOP project. The information of the baseline and outcome measurements will be saved in different databases, and both could be only aggregated by the research members by the birthdate and telephone number of the women.

### Access to data

Research team members from the STOP project will have access to the final pilot trial dataset only for research purposes according to the objectives established in this protocol. We will share the anonymized dataset and output of the statistical analysis openly and transparently on completion of the study providing it in a repository or a supplementary file at the time of submission of the manuscript containing results of the completed study.

### Dissemination policy

We will share the eHealth package with relevant stakeholders in order to upscale it across the EU as well as globally to better combat IPV. Concrete dissemination activities include the production of research papers, guidelines and white papers detailing the eHealth intervention, which will be made available on the STOP project website and presented at relevant professional conferences reaching both health care professionals and other relevant stakeholders and policymakers.

### Consent for publication

All relevant data from this study will be submitted to peer-reviewed journals for publication following the completion of the study in line with sponsor publication policy. Data will be captured for all study participants, and no patient identifiable data will be used in any publications. The sponsor retains the right to review all publications prior to submission or publication. Responsibility for ensuring accuracy of any publication from this study is delegated to the chief investigator. Authorship will be assigned in compliance with International Committee of Medical Journal Editors (ICMJE) guidelines.

The Advisory board is comprised by [name] (Norway), [name] (Denmark), [name] [name] (Spain) and two participant representatives from Denmark and Spain whom prefer to remain anonymous.
